## Secondary analysis

Analyses of secondary endpoints will be conducted to provide supplementary insights to the primary analyses of the study. The secondary endpoints will be analyzed with exploratory intent and will not be adjusted for multiplicity. 1) DAS28-CRP, SDAI, CDAI, at 12, 24, and 36 weeks after intake 2) QOL at 24 weeks after intake (SF-36), 3) ADL at 12, 24, and 36 weeks after intake: mHAQ 4) sonographic examination of joints (scale change) at 12, 24, and 36 weeks after the start of intake will be analyzed in the same way as the primary endpoint. A frequency table will be prepared for each administration group regarding the occurrence of adverse events. In the case of serious adverse events, Kaplan-Meier curves will be generated for survival analysis until the occurrence of the event, and the groups will be compared using Cox proportional hazards model with DAS28-ESR at 0 week as a covariate. For quantitative data on clinical laboratories, summary statistics will be calculated for each time point and the amount of change from before the start of the test food administration for each dose group, and a scatter plot will be created. For other qualitative data, a frequency table should be created for each administration group.

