## Study method

　Eighty female RA patients with moderate disease activity according to the DAS28-ESR will be randomly divided into 40 patients in the propolis group (P group) and 40 patients in the placebo group (C group). P group takes 5 test tablets containing Brazilian propolis (508.5 mg as propolis) per day, and C group takes 5 placebo tablets without Brazilian propolis per day. The DAS28-ESR will be compared in both groups at the time of intervention and after 24 weeks. This will be followed up with a 12-week post-intervention observation period.

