## Dosage and administration of the test food, and duration of administration

　P Group will receive 5 test tablets containing Brazilian propolis daily, and C Group will receive 5 placebo tablets daily. No time of administration is specified. The test food will be provided in sachet packages of five tablets each, with the intention of ingesting five tablets at a time, but it will be acceptable for study participants to ingest them in divided portions. If patients do not take 5 tablets in a day, do not take them the next day and return the whole sachet at next visit. No more than five tablets per day were to be taken. The entire sachet will be collected at each visit, so any leftovers should be checked and recorded at this time. The administration period should be 24 weeks.

［Evidence for setting the dose and duration of administration］

　The dose of the test food containing Brazilian propolis used in this study was 5 tablets (508.5 mg of Brazilian propolis extract powder), which is the midpoint of the 4-6 tablets per day set as the standard dose by Yamada Bee Company, Inc.

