　Subcontractor name: LSI Medience Co.Ltd.

・QOL：SF－36

　　・ADL：mHAQ

・Disease activity：DAS28-ESR・DAS28-CRP・SDAI・CDAI

・Sonographic examination of joints：sonographic examination of synovitis in 7 joints on the side with stronger symptom at baseline (unchanged during the observation period) (2nd and 3rd metacarpophalangeal (MP) joints, 2nd and 3rd proximal interphalangeal (PIP) joints, wrist, and 2nd and 5th metatarsophalangeal (MTP) joints) using both grayscale (GS) (grade 0–3) and power-Doppler (PD) scale (grade 0–3)

Timetable

| Item | pre-  observation | Start administering the test foods | Administration period | End of test food administration | post-  observation |
| --- | --- | --- | --- | --- | --- |
| Period | Before  1-4 weeks | 0 week | After 12 weeks  (±7day) | After 24 weeks  (±7day) | After 12 weeks |
| Medical Examination | 1 | 2 | 3 | 4 | 5 |
| Consent obtain | ○ |  |  |  |  |
| Check patient background | ○ |  |  |  |  |
| Test food administration |  |  |  |  |  |
| Subjective symptoms and other findings | ○ | ○ | ● | ● | ● |
| Observation of adverse events^a^ |  |  | ● | ● | ● |
| Anthropometry^b^ |  | ○ |  | ● |  |
| Blood pressure and pulse measurement |  | ○ | ● | ● | ● |
| Hematological examination |  | ○ | ● | ● | ● |
| Blood Biochemistry Test |  | ○ | ● | ● | ● |
| Sonographic examination of joints |  | ○ | ● | ● | ● |
| QOL assessment |  | ○ |  | ● |  |
| Disease activity assessment^c^ | ○ | ○ | ● | ● | ● |

　Items marked with an asterisk ○ are items to be performed before administration of the test food, and items marked with an ● are items to be performed after administration of the test food.

a: Adverse events are all events that are undesirable, such as side effects, regardless of whether they are causally related to the test food.

b: Measure height, weight, and abdominal circumference as anthropometry.

c: Evaluate DAS28-ESR, DAS28-CRP, SDAI, and CDAI for disease activity.

Blood tests should be performed under fasting conditions to rule out the effects of diet.

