# Discontinuation criteria for individual subjects

　　The principal investigator or sub-investigator will discontinue the study for subjects who are unable to continue the study due to the following reasons, and will take appropriate treatment based on the benefit to the subject. In addition, scheduled surveys/inspections shall be conducted as soon as possible to make a decision (Except in cases where it cannot be conducted due to withdrawal of consent, etc.). If consent is withdrawn after the administration of the study food has begun, it should be made as clear as possible whether the withdrawal is due to ineffectiveness of the study food or an adverse event, or whether it is due to an accidental event (e.g., change of location), and it should be recorded so that it can be used as a reference for the selection of the case for efficacy and safety evaluation. The investigator or sub-investigator should record the date of discontinuation, reason for discontinuation, and comments in the case report form. After discontinuation of the study, if any of the following items 4)-6), 10) are found, hematological and biochemical tests should be performed to confirm safety. In addition, medical examinations will be conducted as deemed necessary by the physician for each symptom. Patients will be followed up for one year after treatment as deemed necessary by the physician according to the examination results. In particular, if the study is discontinued due to the occurrence of an adverse event, follow-up will be conducted until the patient recovers to the original state as much as possible.

1. When the subject declines to participate in the study or withdraws consent
2. Other reasons depending on the subject (e.g., too busy, hospital transfer, relocation)
3. If it is found that the eligibility is not satisfied after registration
4. When it is judged inadvisable to continue administration of the test food due to worsening of the primary disease.
5. If it is difficult to continue the study due to exacerbation of complications
6. If it is difficult to continue the study due to adverse events
7. When pregnancy is detected
8. If the entire study is discontinued
9. If the physician deems it appropriate to stop the study for any other reason.

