## Secondary endpoints

1. DAS28-CRP, SDAI and CDAI at week 12, 24 and 36.
2. QOL evaluated by the change of the score by SF-36 at week 24.
3. The change of ADL evaluated by mHAQ at week 12, 24 and 36.
4. The change of sonographic total scale of hand and foot joint at week 12, 34 and 36.
5. Adverse events requiring discontinuation of the test food up to 24 weeks after starting ingestion.
6. Severe adverse events up to 36 weeks after starting ingestion.
7. All adverse events up to 36 weeks after starting ingestion.

【Evidence of setting】

1） Other methods of assessing disease activity other than the DAS28-ESR, each of which has its own advantages and disadvantages, should also be used.

2) As a general QOL assessment tool for subjects, the SF-36 has been reported in numerous articles due to its simplicity and reliability. We will evaluate the effect of QOL improvement associated with suppression of disease activity.

3) It is the gold standard for the assessment of ADL in RA patients not only in ACR/EULAR but also worldwide. We will evaluate the improvement of ADL with the suppression of disease activity.

4) Obtain a more objective assessment because disease activity assessment includes many subjective items.

5-7) To evaluate the safety of test foods.

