# Statistics Analysis

## Data handling

When compiling data for observation and inspection items specified in the plan by time period, data for inspection items performed on days or at times outside the acceptable range shall be treated as missing. For missing values, LOCF completes the values when the main analysis is performed.

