## Efficacy analysis

The analysis population will be defined as the largest analysis set (full analysis set; FAS), defined as subjects assigned to the study who have consumed the study food at least once and have had at least one efficacy assessment after administration of the study food. Supplemental analyses will also be performed with a per protocol set (PPS) that conforms to the protocol. Hypothesis testing will be two-tailed at the 5% significance level, with two-tailed 95% confidence intervals.

A significance test for the coefficients of the groups will be conducted using a model in which the DAS28-ESR at the end of the intervention for the primary endpoint is the objective variable, the group (control or intervention) is the explanatory variable, and the value of the DAS28-ESR at week 0 is the covariate. In order to confirm the robustness of the results associated with the completion of missing values by LOCF, a mixed-effects model will be used as a supplementary analysis for the primary endpoint. In this case, the normality of the DAS28-ESR at the end of the intervention is checked by histogram, and if normality is not found, the variable is transformed by log transformation or other methods to follow a normal distribution before being used in the analysis. As a secondary analysis, when the objective variable is DAS28-ESR, the interaction between group (control, intervention) and time point (12 weeks, 24 weeks) and between group and time point will be used as explanatory variables, and the analysis will be conducted using a mixed-effects model with the value of DAS28-ESR at week 0 as the covariate and subjects as the variable effect, and the correlation structure of time points will be unstructured.

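### Week-36 secondary analyses inherit LOCF, which for completers fills a missing off-food value with the week-24 on-food value; the effect is small and a short text change removes it

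*Protocol*

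**What the plan says.** Three rules of the Protocol combine.

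- Section 14.1 (Data handling): "For missing values, LOCF completes the values when the main analysis is performed".
- Section 14.2 (Efficacy analysis): the primary analysis regresses end-of-intervention DAS28-ESR on group with the week-0 value as covariate. Because missing values are completed by LOCF, "a mixed-effects model will be used as a supplementary analysis for the primary endpoint". A further mixed-effects model for DAS28-ESR names weeks 12 and 24 as its time points.
- Section 14.3 (Secondary analysis): the secondary measures, the last of them the ultrasound scale, "at 12, 24, and 36 weeks after the start of intake will be analyzed in the same way as the primary endpoint". No exception is made for week 36 and no other missing-data method is named.

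Section 12.2 lists "DAS28-CRP, SDAI and CDAI at week 12, 24 and 36", and also gives mHAQ and the ultrasound scale a week-36 value.

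On treatment state, section 7.4 says "The administration period should be 24 weeks" and section 0.4 adds "This will be followed up with a 12-week post-intervention observation period". In the section 8 timetable, week 24 is headed "End of test food administration", and the next visit is the post-observation visit 12 weeks later.

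**The concern.** For the week-24 primary endpoint, LOCF carries a value forward within the administration period. At week 36 it carries one across the end of intake, so the filled value describes a different treatment state from the one being compared. This is a separate matter from the usual criticism of LOCF.

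Week 36 is the only scheduled off-food comparison after intake. If an effect present at week 24 fades, carried values make part of it appear to remain. The full analysis set requires only one efficacy assessment after intake begins, so a patient last seen at week 12 would also contribute that value at week 36.

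**Working it through.** **Inputs.** From section 15.2: a planned week-24 difference of 0.5, SD 0.78 and 40 per group. From section 14.2: a two-sided 5% test. The documents give neither the share missing at week 36 nor the true week-36 difference, so both are assumed and shown as ranges. DAS28-ESR stands in for the five listed measures. D is written as a positive difference in favour of propolis.

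**The plan's own figure.** n per group = 2 × (1.96 + 0.8416)² × 0.78² / 0.5² = 38.2, rounded up to 39, as stated. A t-based calculation gives 39.2, with power 80.8% at 40. The sample size is not in question.

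**Shift.** Let a share m be missing at week 36, equally in both groups and unrelated to outcome, and filled from week 24.

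- Expected difference under LOCF = (1 − m) × D36 + m × D24
- Shift = m × (D24 − D36)

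**Error rate, no baseline adjustment, D36 = 0.** SE = 0.78 × √(2/40) = 0.1744; b = 0.5m / 0.1744; rejection = Φ(−1.96 + b) + Φ(−1.96 − b).

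| m | patients per group | shift, D36 = 0 | shift, D36 = 0.25 | rejection, D36 = 0 |
|---|---|---|---|---|
| 2.5% | 1 | 0.0125 | 0.006 | 5.06% |
| 5% | 2 | 0.025 | 0.0125 | 5.24% |
| 10% | 4 | 0.05 | 0.025 | 5.95% |
| 20% | 8 | 0.10 | 0.05 | 8.84% |

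If D36 = 0.5, the shift is zero at every m.

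**Mixed sources.** Suppose half of the filled values come from week 12 or from early stopping and carry only 0.25. With D36 = 0 the shift is m × (0.5 × 0.5 + 0.5 × 0.25) = 0.375m, that is 0.009, 0.019, 0.038 and 0.075. Rejection is 5.03%, 5.13%, 5.53% and 7.14%.

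**With baseline adjustment.** Simulation, 20,000 runs per m, correlation 0.5 between visits (assumed), differences of 0.5 at weeks 12 and 24 and 0 at week 36:

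| m | ANCOVA with LOCF: mean difference | ANCOVA with LOCF: rejection | mixed model, weeks 12/24/36: rejection |
|---|---|---|---|
| 2.5% | 0.013 | 5.0% | 4.7% |
| 5% | 0.023 | 5.2% | 4.7% |
| 10% | 0.051 | 6.3% | 4.7% |
| 20% | 0.099 | 9.6% | 4.7% |

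The mixed model's mean error is about 0.001 throughout. At m = 20% its standard error is 0.168 against 0.155 for LOCF, a ratio of 1.08.

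**The case against.** **Reading.** A reader might infer that the protocol orders LOCF at week 36. It does not say so. Section 14.1 ties LOCF to the main analysis, and the same-way clause in 14.3 could mean only the baseline-adjusted model. That narrower reading is possible. It is less natural, because 14.2 treats LOCF completion as part of how the primary endpoint is analysed and 14.3 offers nothing in its place. If it is what was meant, week 36 simply has no missing-data rule in this document, which a separate analysis plan could supply.

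**Robustness check.** If the same-way clause imports LOCF, it may equally import the supplementary mixed-effects model, so it would be wrong to say that these endpoints have no check at all. However, the only time points that 14.2 names for a mixed model are weeks 12 and 24. As written, it does not address week 36.

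**Source of the filled value.** It would be too strong to say that every filled value is on-food. Section 9 asks, for patients who discontinue, that "scheduled surveys/inspections shall be conducted as soon as possible". The value carried from an early stopper may therefore itself be partly or wholly off-food. The on-food claim holds for completers.

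**Size.** Section 15.2 expects few dropouts. The larger error rates need 20% missing and complete loss of the planned effect, and the documents support neither. Section 8 gives ±7-day windows for weeks 12 and 24 but none for week 36, so the out-of-window rule has no stated limit there that would add missing values. The measures are exploratory and unadjusted for multiplicity, so a small change in one nominal error rate alters no claim the protocol makes. No hypothesis of persistence is stated. All of this stands, and it limits the weight of the point.

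**Scale.** No figure above is on the SDAI, CDAI, mHAQ or ultrasound scale. The formula carries over, though: on any scale, the shift is the share m of whatever effect has been lost since week 24.

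**Conclusion.** The point holds as a minor one. On the natural reading of sections 14.1 to 14.3, the leading week-36 analyses of the five measures fill missing off-food values by LOCF, for completers from the last on-food visit, and so pull the week-36 difference towards the on-food one.

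At the low dropout the protocol expects, taken here as 2.5% to 5% missing, the pull is about 0.01 to 0.025 DAS28 points if the effect has gone, half that if half of it remains, and nil if it persists. This assumes the planned 0.5 at week 24, missingness unrelated to outcome and equal between groups, and filling from week 24.

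The documents do not support reading this as a threat to the trial's conclusion. The primary analysis is at week 24, and SF-36 is assessed only at weeks 0 and 24.

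**What to change.** Add to section 14.3:

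> LOCF does not carry values from the administration period into week 36. For DAS28-CRP, SDAI, CDAI, mHAQ and the sonographic scale, the week-36 group difference is estimated from observed values with the mixed-effects model of 14.2, with weeks 12, 24 and 36 as time points and the week-0 value as covariate.

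Naming the five measures keeps SF-36 out, since it has no week-36 assessment. The text settles the matter under either reading of 14.1.

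The change needs two sentences and no extra patients, visits or measurements. It rests on a missing-at-random assumption, and its standard error is slightly larger (about 8% at 20% missing). Weeks 12 and 24 would still be led by ANCOVA with LOCF, so a reported time course would mix two methods. Showing the mixed model's own estimates for all three weeks alongside avoids that, because the model already contains them.

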# Observation and examination items and schedule

The following surveys will be conducted according to the timetable

1. Patient's background

　Medical record number, patient name, gender, date of birth, comorbidities, medical history, current medical history, previous treatment, concomitant medications (concomitant therapy and current treatment details), lifestyle (smoking status, alcohol consumption, exercise habits, sleep time, supplement use and type). However, medical record numbers and patient names are not entered into the REDCap (case report form).

1. Confirmation of intake of test foods

　The intake status during the study period will be assessed in percentage and recorded in REDCap. Participants will return all samples, including unused packaging materials, to the implementing medical institution at each visit. The CRC calculates the intake rate based on the number of tablets distributed and returned. For each case, the intake of the test food from the day after the previous visit to the day of the visit will be investigated and compliance with the intake will be requested.

1. Confirmation of subjective symptoms and other findings, evaluation of disease activity

Based on the questionnaire, palpation, and laboratory data, disease activity is quantified according to the following formula.

DAS28-ESR = 0.56 × √28TJC + 0.28 × √28SJC + 0.76In(ESR) + 0.014 × GH-VAS

DAS28-CRP = 0.56 × √28TJC + 0.28 × √28SJC + 0.36In(CRP × 10 + 1 ) + 0.014 × GH-VAS + 0.96

SDAI = 28TJC + 28SJC + PtGH-VAS(patient) + DrGH-VAS(physician) + CRP (mg/dl)

CDAI = 28TJC + 28SJC + PtGH-VAS(patient) + DrGH-VAS(physician)

1. Confirmation of adverse events and side effects: Describe in the medical record and case report the details, including abnormalities in various laboratory data, time of occurrence and disappearance, severity, treatment, outcome, assessment of severity, and relationship to the study food, and follow up as necessary. The severity is defined as 1) mild: administration can be continued without treatment, 2) moderate: administration can be continued with some treatment, and 3) severe: administration should be stopped or discontinued.
2. Height, weight, and waist circumference
3. Blood pressure and pulse rate
4. Hematological tests

WBC, RBC, Hb, Ht, Plt

1. Blood biochemistry test

AST, ALT, γ-GTP, T-Bil, Cre, BUN, CRP, ESR, RF, TP, Alb, T-chol, HDL-chol,TG, Na, Cl, K, Mg, P, Ca, FBS

1. Other specific tests

・anti-CCP antibody、MMP-3、IL-6、IL-17、IL-10

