## Serious adverse event reporting

　A "serious adverse event" is defined as any unfavorable medical event, regardless of dose, that meets the following criteria

(1) Lethal events

(2) Life threatening

(3) Events that require hospitalization for treatment

(4) Permanent or significant disability or malfunction

(5) Those that cause congenital anomalies in the offspring

If the principal investigator recognizes the occurrence of a serious adverse event while conducting an invasive study, the principal investigator shall promptly report all serious adverse events to the hospital director (Clinical Trial Review Committee in the case of Osaka City University), regardless of whether or not there is a causal relationship with the study, and shall also report to the responsible physician of the other medical institution if a causal relationship between the study and the serious adverse event cannot be ruled out in a multicenter study.

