## Interim analysis

The food to be administered is a health food that is already sold worldwide and is unlikely to cause serious adverse events. In addition, it is not a powerful drug, so it is unlikely that the effect will appear in a short period of time. Since the total administration study period is 24 weeks, we believe that there is little merit in conducting an interim analysis and will not conduct an interim analysis.

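### Secondary endpoint 6 counts severe adverse events but section 14.3 models serious ones, and the Cox comparison planned for them is undefined or very imprecise with 40 patients per arm

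*Protocol*

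**What the plan says.** Protocol section 12.2 lists three safety endpoints. Endpoint 5 is "Adverse events requiring discontinuation of the test food up to 24 weeks after starting ingestion". Endpoint 6 is "Severe adverse events up to 36 weeks after starting ingestion". Endpoint 7 is all adverse events to week 36.

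Section 8 grades every adverse event by whether the test food can continue. Mild means it can continue without treatment, moderate that it can continue with some treatment, and the top grade is "severe: administration should be stopped or discontinued".

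Section 10.2 treats seriousness as a separate concept. A serious adverse event "is defined as any unfavorable medical event, regardless of dose, that meets the following criteria", followed by a list: death, threat to life, hospitalization for treatment, permanent or significant disability, congenital anomaly. Reporting is required whatever the cause.

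Section 14.3 gives two layers of safety analysis. The first covers all adverse events: "A frequency table will be prepared for each administration group regarding the occurrence of adverse events". The second is reserved for serious ones: "In the case of serious adverse events, Kaplan-Meier curves will be generated for survival analysis until the occurrence of the event", after which "the groups will be compared using Cox proportional hazards model with DAS28-ESR at 0 week as a covariate". The same section calls the secondary analyses exploratory and makes no adjustment for multiplicity.

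No section states an expected number or rate of serious events. Section 14.4 says only that the food is "unlikely to cause serious adverse events".

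**The concern.** There are two separate problems.

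The endpoint and its analysis name different events. An unrelated hospitalization is serious but need not be graded severe. An event that stops intake is severe by section 8 but need not be on the list in 10.2. The two readings of endpoint 6 can therefore give different counts from the same data. If the choice is still open when results are known, it can be made in their light.

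The only between-group model for safety is a Cox regression in a trial of 80 patients. A hazard ratio needs events in both arms. If serious events are few, the model may give no finite estimate, or an interval too wide to use, while the frequency table beside it has no stated confidence limits.

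**Working it through.** **Terms, side by side**

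| | Severe | Serious |
|---|---|---|
| Defined in | Section 8, by stopping administration | Section 10.2, by outcome |
| Named endpoint in 12.2 | Endpoint 6, to week 36 | None |
| Analysis in 14.3 | General frequency table | Kaplan-Meier and Cox |

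Up to week 24, a severe event in the sense of section 8 is nearly the same as an event requiring discontinuation, which is endpoint 5. After week 24 nothing is administered (section 7.4 and the timetable in section 8). All three grades are worded by whether administration can continue, so an event that begins in weeks 24 to 36 has no workable grade.

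**Inputs for the Cox comparison**

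- 40 patients per arm (section 15.2). The section's own sample size reproduces: 2 × (1.96 + 0.8416)² × 0.78² / 0.5² = 38.2, so 39 per group. The safety point does not affect it.
- No event rate is stated. Assumed 36-week risks p from 1% to 10% per arm, equal in both arms, with no dropout.

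**Chance of an arm without events**

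Let q = (1 − p)^40 be the chance that one arm has no event. The group coefficient has no finite maximum likelihood estimate unless both arms have at least one event, so the failure probability is 1 − (1 − q)². For p = 2%: q = 0.98^40 = 0.446, and 1 − 0.554² = 0.693.

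| p per arm | Events expected (80p) | Neither arm has an event, q² | Only one arm has events, 2q(1 − q) | No finite hazard ratio |
|---|---|---|---|---|
| 1% | 0.8 | 45% | 44% | 89% |
| 2% | 1.6 | 20% | 49% | 69% |
| 3% | 2.4 | 9% | 42% | 50% |
| 5% | 4.0 | 2% | 22% | 24% |
| 10% | 8.0 | below 0.1% | 3% | 3% |

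The failure probability is exactly one half at p = 3.02%, or about 2.4 events in total. With unequal risks it is 52% for 2% versus 5%, and 71% for 1% versus 5%.

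**Check by simulation**

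A Cox model with group and baseline DAS28-ESR was applied to 400 simulated trials per rate (constant hazard over 36 weeks, baseline uniform on 3.2 to 5.1). An arm had no event in 90%, 68%, 49%, 25% and 4% of trials at 1%, 2%, 3%, 5% and 10%. Where both arms had events, fits failed in only 0.25% of trials at 1% and in none at the other rates. The empty arm is the cause, not the covariate.

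**Precision when an estimate exists**

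- In the simulation, a further 48% of trials at 5%, and 15% at 10%, had a standard error of the log hazard ratio above 1.
- Eight events split 4/4 give a standard error of about √(1/4 + 1/4) = 0.71. Around a hazard ratio of 1 the 95% interval is exp(±1.96 × 0.71), about 0.25 to 4.0.
- 80% power needs 66 events (Schoenfeld) or 71 (Freedman) for a hazard ratio of 2, and 27 or 32 for a hazard ratio of 3. With 4 events power is about 10% and 20%; with 8 events, 16% and 34%.

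**What an exact summary gives**

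For 0 events in 40, the two-sided 95% Clopper-Pearson upper limit is 1 − 0.025^(1/40) = 8.8%. Such a limit exists for any count.

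**The case against.** The strongest reply is that little is lost. The analysis is exploratory, the trial's aim is disease activity, and no safety hypothesis or margin is stated. Section 8 requires severity to be recorded for each event, and 14.3 tabulates adverse events by arm. Severe events can therefore be counted, and exact limits can be worked out from the table. If only one arm has events, a likelihood-ratio test and a one-sided profile-likelihood bound still exist. Handling of sparse data is often left to the SAP. The choice of words may be a translation slip. All of this stands, and it limits the weight of the point. It does not remove the contradiction between 12.2 and 14.3, and the Cox model is something the protocol itself fixes.

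A reader might also infer more than the text supports:

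- That severe events are never analysed. They have the frequency table; what they lack is a dedicated comparison.
- That endpoint 6 simply duplicates endpoint 5. It runs to week 36, not week 24.
- That section 14.4 forecasts almost no serious events. It speaks of events the food causes, as a reason for having no interim analysis. Section 10.2 counts events of any cause, including hospitalization, in patients who may be taking biologics and steroids. A background risk of 5% or more cannot be excluded.
- That the Cox model will usually fail. This holds only below about 3% per arm.
- That the covariate is to blame. It adds a second coefficient to very few events, but an empty arm breaks the comparison with or without it.

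**Conclusion.** The mismatch of terms is certain from the text: endpoint 6 and the time-to-event analysis refer to differently defined events, and the severity grade cannot be applied as written to events that begin after week 24.

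The point about the Cox model is conditional, because the event rate is an assumption. With 40 per arm, equal risks and no dropout, the hazard ratio is not estimable in most trials below about 3% per arm. At 5% to 10%, only 4 to 8 events are expected in total, and the estimate is very imprecise even when it exists. Throughout the assumed 1% to 10% range, it is a poor choice as the main between-group safety summary. The primary analysis and sample size are unaffected. The change is worth making because it settles a named safety endpoint at almost no cost, not because a trial conclusion depends on it.

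**What to change.** 1. Reconcile 12.2 and 14.3 so that endpoint 6 and its analysis use the same term. The intended one is presumably serious adverse events as defined in 10.2, since severe as defined largely overlaps endpoint 5; the sponsor must confirm this. If severe is kept, sections 8 and 12.2 must be reconciled for weeks 24 to 36.
2. In 14.3, make the main between-group summary the number and percentage of patients with at least one such event per arm, with Clopper-Pearson limits, and an exact confidence interval for the risk difference. This replaces the Cox comparison.
3. Keep the Kaplan-Meier curves as description.

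The cost is a few words in 12.2 and 14.3, made before unblinding, with no new data or patients. The small downside is that time-to-event information becomes descriptive only.
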